#### Statistical analysis plan

A full SAP will be produced prior to the analysis of any data. The SSC will be given the opportunity to comment on the SAP prior to it being signed-off by the CI and lead statistician.

#### Additional analyses

An adjusted analysis will also be conducted adjusting for the corresponding baseline measure using a general linear model. A similar analysis to the OBV and sulcus measurement analysis will be used for the TDI score from the Sniffin’ Sticks psychophysical smell test and the ODQ. If the assumptions of the tests are not met, then non-parametric approaches will be used. We will also assess the correlation between the OBV measurements and the TDI scores using Pearson’s correlation coefficient.

#### Analysis population

The intention-to-treat population will consist of all participants who were randomised who have outcome data in the group that they were allocated to, regardless of adherence. No multiple imputation will be undertaken for this study.

#### Missing data

Patterns of missing data will be described, but no imputation will be undertaken in this early phase study.

### Data monitoring

Details of the committee personnel can be found in Fig. 1 in  Appendix.

#### Data monitoring oversight

The trial will be led by the chief investigator working with the co-applicants who provide expertise in statistics, methodology, data management, functional imaging, and computational modelling. A research associate (RA) will be employed to undertake the day-to-day running of the study. Study activities and responsibilities will be documented in an overarching trial management agreement and signed by the James Paget University Hospital, CI, and the Clinical Research Network. The RA will maintain essential documentation with a study Master File and the CI will manage the regulatory and ethics approval process.

The Project Management Group (CI, RA, research nurse, other co-applicants as needed) research team will meet regularly (monthly during the setup phase then 2 monthly during the recruitment phase) to draft, review, and approve key essential documents including any documentation needed for research governance. The study steering committee will meet twice a year and include all co-applicants and affiliated research team members including our PPI representative. Online meeting platforms will be used where needed. Ad hoc meetings will be added where needed for any issues arising including safety monitoring. The Independent Steering Committee will encompass the role of a safety committee for the purposes of this trial.

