#### Blinding (masking)

All participants, care providers, and outcome assessors will be blinded to the treatment allocation. Accidental unblinding will be logged and monitored to ensure that appropriate steps are taken to prevent this from reoccurring. The data analysts will not be blinded as they are required to know the group for the preparation of the DMEC reports.

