#### Indications for trial closure

The trial may be stopped before completion for the following reasons:On the recommendation of the SSC (Study Steering Committee)On the recommendation of the sponsor and CIAt request from the funder

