#### Adverse event reporting and monitoring

Definitions of harm of the EU Directive 2001/20/EC Article 2 based on the principles of ICH GCP apply to this trial. We will notify the REC and sponsor of any unexpected serious adverse reactions. We will adhere to the Health Research Authority guidelines [88].

All adverse events will be recorded in the database, to monitor for harm and allow for an ongoing comparison between arms for the data monitoring and safety committee in any subsequent RCT. All non-serious AEs and ARs, whether expected or not, should be recorded in the patient’s medical notes and reported in the database. Serious Adverse Events (SAEs) and Serious Adverse Reactions (SARs) must be notified to NCTU and the sponsor within 24 h. When an AE or AR occurs, the investigator responsible for the care of the participant must first assess whether the event is serious. If the event is classified as ‘serious’ then it will be reported in an expedited manner using the study-specific reporting form. The CI (or delegate) will assess whether the event could be related to trial treatment.

If there is at least a possible involvement of the trial intervention (including placebo), the CI must assess the expectedness of the event. An unexpected adverse reaction/event is one that is not reported in the approved version of the Reference safety Information (RSI) in the Vitadral SmPC, or one that is more frequently reported or more severe than previously reported. If a SAR is assessed as being unexpected it becomes a SUSAR (suspected, unexpected, serious adverse reaction) and REC reporting guidelines apply. If the sponsor and CI deem the event relevant, it will also be reported to the MHRA via their Yellow Card scheme.

The SSC in their role as Safety Committee will be provided with all safety data, along with the corresponding treatment arm, by the trial statistician. The committee can advise that the trial is stopped early in the unlikely event that there are concerns of harm to the participants.

We will withdraw any female participant who becomes pregnant. Female participants will be asked to inform the RA if they become pregnant during the course of the study.

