#### Independent study steering committee

The Independent Study Steering Committee (SSC) will include two experienced physicians independent of the trial and is the independent group responsible for oversight of the study in order to safeguard the interests of participants. The SSC provides advice to the CI, NCTU, the funder, and sponsor on all aspects of the trial. The membership, frequency of meetings, activity (including trial conduct and data review), and authority will be covered in the SSC terms of reference. Due to the nature of the trial proposed, the SSC will incorporate the role of a safety committee as defined below:To detect any trends, such as increases in un/expected events, and take appropriate actionTo seek additional advice or information from investigators where requiredTo evaluate the risk of the trial continuing and take appropriate action where necessary

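### SSC membership is stated inconsistently; under one stated membership, staff meant to stay blinded would sit on the committee that receives safety data by arm

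*Protocol article*

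**What the plan says.** Five parts of the protocol article bear on this.

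- **Data monitoring oversight**, on membership: "The study steering committee will meet twice a year and include all co-applicants and affiliated research team members including our PPI representative". The same section closes with: "The Independent Steering Committee will encompass the role of a safety committee for the purposes of this trial".
- **Indications for trial closure** expands the abbreviation: "On the recommendation of the SSC (Study Steering Committee". The abbreviation list gives the same expansion and no other.
- **Independent study steering committee** says that the SSC will have two physicians from outside the trial, and that it "is the independent group responsible for oversight of the study in order to safeguard the interests of participants". It also gives the SSC the safety-committee role. The Discussion repeats the description of the SSC as independent.
- **Adverse event reporting and monitoring**, on what the committee sees: "The SSC in their role as Safety Committee will be provided with all safety data, along with the corresponding treatment arm, by the trial statistician".
- **Blinding (masking)**: "All participants, care providers, and outcome assessors will be blinded to the treatment allocation". One exemption follows: "The data analysts will not be blinded as they are required to know the group for the preparation of the DMEC reports".

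Separately, the section Study management group places the study team, the other co-applicants and a patient representative in the SMG.

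**The concern.** The committee that receives safety data by arm is described in one place as containing the people who run the trial, and in others as independent of it. A reader setting up the committee from this text could follow either account.

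The difference matters because the trial is presented as double-blinded. The allocation section relies on pack identifiers so that team members can dispense without knowing the arm. The chief investigator or a delegate decides whether an adverse event could be related to treatment, and the chief investigator judges expectedness. These are the people whom the broad membership would admit to the by-arm data. Judgements of causality are open to influence once the arm is known. Exposure during conduct cannot be undone afterwards.

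**Working it through.** No figure is at stake, so the check sets the statements side by side.

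1. **Who receives by-arm data?** The SSC, acting as safety committee, from the trial statistician (Adverse event reporting and monitoring).
2. **What is the SSC?** The Study Steering Committee (Indications for trial closure; abbreviation list). The sections Independent study steering committee and Discussion use the same name and abbreviation with the word independent in front. If two separate committees were intended, the text does not distinguish them.
3. **Who sits on it?** Data monitoring oversight says every co-applicant and the associated research staff. The preceding sentence of that section describes the research team as the chief investigator, research associate, research nurse and other co-applicants, so the natural reading includes the first two of these.
4. **Does the independent description exclude them?** No. The section Independent study steering committee says the SSC will include two outside physicians. It does not limit membership to outsiders. Yet a committee holding all co-applicants and research staff cannot also be the independent oversight group that the same section describes. The two accounts conflict, and neither overrides the other.
5. **Who must stay blinded?** Participants, care providers and outcome assessors, with only the data analysts exempt (Blinding). The allocation section requires blinded dispensing.
6. **Which roles would be exposed under the broad membership?**
   - The research associate dispenses the drops (Arm A, Arm B).
   - The chief investigator or a delegate judges relatedness (Adverse event reporting and monitoring). Emergency unblinding treats the chief investigator's access to an individual's arm as an audited exception, which implies blinding otherwise.
7. **What do the documents leave open?**
   - No section names who measures olfactory bulb volume.
   - No section names who runs the 3-month smell test. The one smell test assigned to the research associate is the baseline test under telephone screening (Recruitment), and allocation comes only after baseline measures are complete.
   - Twice a year is the meeting frequency of the committee described in Data monitoring oversight. No schedule is given for by-arm reports, and the section Independent study steering committee leaves its meeting frequency to the terms of reference.
   - Nothing says whether the reports are event listings or summary tables.

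Steps 1 to 5 establish the contradiction. Step 6 shows what follows if the broad membership is applied. Step 7 marks where the inference has to stop.

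**The case against.** The strongest reply is that the text, read as a whole, points to an independent recipient. The closing sentence of Data monitoring oversight, the section Independent study steering committee and the Discussion all attach independence to the body in question, and the first two give that body the safety role. The SMG section already houses the co-applicants, and the Discussion separates management by the SMG from oversight by the SSC. On this view the broad membership sentence is an outlier, probably a naming slip, and not a decision to unblind the team. Committee personnel are referred to a figure that is not shown, and the SSC's membership and data review are left to its terms of reference. An article may reasonably leave closed-session rules to that document.

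Much of this stands. The independent reading is the more likely intention, and the lack of a described closed session is not a fault in itself. It does not remove the conflict, because the article states a membership rule that contradicts its own description of the same committee. A figure listing members would not reconcile the two sentences.

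A reader might go further and infer that the double blind is broken, that all outcome assessors see by-arm data twice a year, or that volume segmentation and smell-test scores will be biased. The documents do not support this. The assessors are not identified, the frequency and form of the by-arm reports are not given, and the research associate's documented smell test precedes the participant's randomisation. Matching an event to a participant in a trial of 57 would also require event-level listings, which are not specified.

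**Conclusion.** The concern holds as an internal contradiction over SSC membership with a conditional consequence. If the membership in Data monitoring oversight were applied, staff who dispense the drops or judge causality could see safety data by arm, contrary to the Blinding and allocation sections. If by-arm data went only to the independent members, the blind would be kept. The article does not settle which applies.

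This rests on two readings: that Study Steering Committee and Independent Study Steering Committee are the same body, as the shared abbreviation indicates, and that the research staff named as members include the research associate and chief investigator. The size of any bias cannot be derived from the document. The point still deserves correction before by-arm data are circulated, because the trial's blinding should not depend on which sentence is followed.

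**What to change.** Reconcile three sections of the protocol.

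- **Data monitoring oversight:** remove co-applicants and research team members from the membership of the committee that receives by-arm data. The SMG section already gives them a place, and the sentence could be reworded to refer to the SMG.
- **Adverse event reporting and monitoring:** state that arm-identified safety data go only to SSC members independent of the trial, in closed session. Everyone else sees pooled data, apart from the analysts who prepare the reports and are already exempt from blinding.
- **Independent study steering committee:** state the same restriction, use one name for the committee throughout, and carry the rule into the SSC terms of reference. The Blinding section's reference to DMEC reports should be aligned with that name, since the safety role is assigned to the SSC.

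The cost is wording and the terms of reference. No extra members are needed to begin, because two independent physicians are already planned for the SSC.

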#### Indications for trial closure

The trial may be stopped before completion for the following reasons:On the recommendation of the SSC (Study Steering Committee)On the recommendation of the sponsor and CIAt request from the funder

#### Adverse event reporting and monitoring

Definitions of harm of the EU Directive 2001/20/EC Article 2 based on the principles of ICH GCP apply to this trial. We will notify the REC and sponsor of any unexpected serious adverse reactions. We will adhere to the Health Research Authority guidelines [88].

All adverse events will be recorded in the database, to monitor for harm and allow for an ongoing comparison between arms for the data monitoring and safety committee in any subsequent RCT. All non-serious AEs and ARs, whether expected or not, should be recorded in the patient’s medical notes and reported in the database. Serious Adverse Events (SAEs) and Serious Adverse Reactions (SARs) must be notified to NCTU and the sponsor within 24 h. When an AE or AR occurs, the investigator responsible for the care of the participant must first assess whether the event is serious. If the event is classified as ‘serious’ then it will be reported in an expedited manner using the study-specific reporting form. The CI (or delegate) will assess whether the event could be related to trial treatment.

If there is at least a possible involvement of the trial intervention (including placebo), the CI must assess the expectedness of the event. An unexpected adverse reaction/event is one that is not reported in the approved version of the Reference safety Information (RSI) in the Vitadral SmPC, or one that is more frequently reported or more severe than previously reported. If a SAR is assessed as being unexpected it becomes a SUSAR (suspected, unexpected, serious adverse reaction) and REC reporting guidelines apply. If the sponsor and CI deem the event relevant, it will also be reported to the MHRA via their Yellow Card scheme.

The SSC in their role as Safety Committee will be provided with all safety data, along with the corresponding treatment arm, by the trial statistician. The committee can advise that the trial is stopped early in the unlikely event that there are concerns of harm to the participants.

We will withdraw any female participant who becomes pregnant. Female participants will be asked to inform the RA if they become pregnant during the course of the study.

#### Quality assurance and control

The Quality Assurance (QA) and Quality Control (QC) considerations for the APOLLO trial are based on the standard NCTU Quality Management Policy that includes a formal Risk Assessment, and that acknowledges the risks associated with the conduct of the trial and proposals of how to mitigate them through appropriate QA and QC processes. Risks are defined in terms of their impact on the rights and safety of participants; project concept including trial design, reliability of results, and institutional risk; project management; and other considerations.

NCTU staff will review Case Report Form (CRF) data for errors and missing key data points. The trial database will also be programmed to generate reports on errors and error rates. Essential trial issues, events, and outputs, including defined key data points, will be detailed in the APOLLO trial Data Management Plan.

A Quality Management and Monitoring Plan (QMMP) will detail monitoring and IMP accountability procedures.

#### Study team

A research associate (RA) will be employed to undertake the day-to-day running of the study. A Senior Trial Manager (STM) at Norwich CTU will assist the CI and RA with study planning, study set-up prior to the appointment of the RA, oversight of study management, and adherence to CTU practices. The STM provides expertise in trial design, methodology, and conduct throughout the project. A Senior Statistician at Norwich CTU will provide advice throughout the study and statistical oversight and will be supported by a project statistician throughout the study.

#### Study management group

A study management group (SMG) will be set up to assist with developing the design, co-ordination, and strategic management of the trial. The SMG includes the members of the Study Team as well as other co-applicants who provide expertise in statistics, methodology, data management, functional imaging, computational modelling, and an independent PPI representative. The membership, frequency of meetings, activity (including trial conduct and data review), and authority will be covered in the SMG terms of reference.

The SMG will meet regularly (monthly during the setup phase then 2 monthly during the recruitment phase) to draft, review, and approve key essential documents including any documentation needed for research governance.

#### Independent study steering committee

The Independent Study Steering Committee (SSC) will include two experienced physicians independent of the trial and is the independent group responsible for oversight of the study in order to safeguard the interests of participants. The SSC provides advice to the CI, NCTU, the funder, and sponsor on all aspects of the trial. The membership, frequency of meetings, activity (including trial conduct and data review), and authority will be covered in the SSC terms of reference. Due to the nature of the trial proposed, the SSC will incorporate the role of a safety committee as defined below:To detect any trends, such as increases in un/expected events, and take appropriate actionTo seek additional advice or information from investigators where requiredTo evaluate the risk of the trial continuing and take appropriate action where necessary

### Trial sponsor

The University of East Anglia is the trial sponsor. The role of the sponsor is to take on responsibility for securing the arrangements to initiate, manage, and finance the trial. The Sponsor is responsible for ensuring that the study meets the relevant standards and makes sure that arrangements are put and kept in place for management, monitoring, and reporting. The University of East Anglia has delegated some Sponsor’s activities to the CI and NCTU, these are documented in the collaboration agreement and delegation of responsibilities.

## Ethics and dissemination

### Research ethics approval

Before initiation of the trial at any clinical site, the protocol, all informed consent forms and any material to be given to the prospective participant will be submitted to the relevant ethics committee for approval. Any subsequent amendments to these documents will be submitted for further approval.

The rights of the participant to refuse to participate in the trial without giving a reason must be respected. After the participant has entered the trial, the clinician remains free to give alternative treatment to that specified in the protocol, at any stage, if s/he feels it to be in the best interest of the participant. The reasons for doing so must be recorded. After randomisation, the participant must remain within the trial for the purpose of follow-up and data analysis according to the treatment option to which they have been allocated. However, the participant remains free to change their mind at any time about the protocol treatment and follow-up without giving a reason and without prejudicing their further treatment. The study has received approval from the West Midlands–Black Country Research Ethics Committee, reference number 21/WM/0179. The study has also received Health Regulation Authority approval and all sites will be required to provide confirmation of capacity and capability before recruitment starts.

### Competent authority approvals

The APOLLO trial is not a Clinical Trial of an Investigational Medicinal Product (IMP) as defined by the EU Directive 2001/20/EC. Therefore, a CTA is not required in the UK.

### Confidentiality

Any paper copies of personal trial data will be kept at the participating site in a secure location with restricted access. Confidentiality of patient’s personal data is ensured by not collecting patient names on CRFs and limiting access to personal information held on the database at NCTU. At trial enrolment, the patient will be issued a participant identification number and this will be the primary identifier for the patient, with secondary identifiers of month and year of birth and initials.

The patient’s consent form will carry their name and signature. These will be kept at the trial site, a copy may be sent to NCTU for monitoring purposes. This copy will be destroyed once checks are complete. Consent forms will not be kept with any additional patient data.

